#### Laboratory sample collection, storage and transportation

From each eligible individual 5ml of venous blood will be collected at baseline and at the end of the intervention.The serum will be separated from whole blood by collection tubeThe serum will be transported to Nunc tube for storage and transportationThe serum will be stored in deep freezer at below -80°C until transportation and analysisCollected samples will be transported to Bahir Dar University Teaching Hospital department of laboratory by using vaccine carrierFinally, the laboratory measurement will be done by those special trained personnel at Bahir Dar University Teaching Hospital department of laboratory.

### Statistical analysis

The analysis will follow modified intention-to-treat principles (based on group randomized to and using all available data but without being able to directly assess the impact of the intervention being offered to those for whom we do not have follow-up data and where their outcome data are not missing at random). Descriptive statistics means (standard deviations), medians (interquartile ranges), frequencies (relative frequencies) will be used to summarize participant’ characteristics and study outcomes. Epi Data (double entry) will be used to enter the quantitative data and it will be analyzed using Stata 13.1 or later versions, with p<0.05 considered significant. Generalized linear mixed models (GLMM) will be used to assess the impact of the intervention on the change of metabolic syndrome components, as well as on the knowledge, attitudes and practice of participants on healthy lifestyle. The metabolic syndrome indicators (Obesity level, BP, FG, HDL, and TGL), knowledge, attitudes, and practices towards lifestyle and cardiovascular risk factors will be the outcome variables, and age, sex, marital status, educational status, work experience, working hours per day, monthly income, religion, health condition, and level of KAP will be the independent variables of the study.

All items in the CONSORT statement will be followed when reporting, and a CONSORT flow diagram will be included to indicate participant flow and, if available, the causes of exclusion and loss to follow-up (**Fig 1)**. The effectiveness of the intervention will be assessed using differences in changes in the metabolic syndrome indicators (Obesity level, BP, FG, HDL, and TGL) between groups from baseline to nine months. As well as, by assessing knowledge, attitudes, and practices towards lifestyle and cardiovascular risk factors before and after the intervention as well as between the control and intervention groups.

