**Methods and analysis:**

This randomized controlled trial will be implemented with 226 bank employees (age ≥18 years) with metabolic syndrome from government and private banks in Bahir Dar City, Ethiopia. Participants will be randomized to intervention (education) and control (general health advice) groups. The intervention group will be given one-on -one base education about healthy diets, physical exercise, stress management, avoidance of harmful alcohol consumption and smoking cessation by experts on health promotion. Text messages will be sent every two weeks and reading materials will also be provided. Additionally, a review meeting will be held at the 3^rd^ and 6^th^ month of the intervention. The primary outcomes of interest will be change in metabolic parameters (obesity levels, blood pressure, fasting blood glucose, total cholesterol, high density lipoprotein, low density lipoprotein, and triglycerides). Secondary outcomes will be knowledge, attitudes and practice of the participants towards lifestyle and cardiovascular risk factors, feasibility, acceptability, implementation fidelity, and cost-effectiveness of the intervention. Data will be collected at three time points: at baseline, at the 6^th^ month of the intervention and at the end of the intervention (9 months). Generalized linear mixed models will be utilized to compare the desired outcome between the trial arms, after accounting for baseline variations. Cost-benefit analysis and a qualitative process evaluation of the intervention will also be conducted.

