### Sample size

Because researchers can use mean and standard deviation (SD) from previous studies in a similar context to estimate sample size [26]. We utilized the mean and SD from a study at Jimma University among university staff to evaluate the effectiveness of behavior change communication on metabolic syndrome among Ethiopian adults in a randomized controlled trial [27]. The sample size for this randomized control trial study was determined under the assumptions and using the formula of the sample size calculation for randomized control trial studies with continuous outcome variables [26]. Since blood pressure is the study’s primary outcome measure and the most common indicator of metabolic syndrome among bank employees in Bahir Dar city and also gives a maximum sample size among other indicators, the means and standard deviations of systolic blood pressure were taken from a study with a similar design that was conducted in Ethiopia [27], and a power of 80%, a 1:1 ratio, and a 95% confidence interval were used. Then the sample size was calculated as follows;

$$n1=\frac{(\sigma 1^{2}+\sigma 2^{2}){\;[Z1‐\alpha /2+Z\;1‐\beta ]}^{2}}{{\left(M1‐M2\right)}^{2}}$$

$$n1=\frac{(15.0^{2}+16.3^{2})\;{\left[1.96+0.84\right]}^{2}}{{\left(107.8‐114.2\right)}^{2}}=\frac{(225+265.69)\;{\left[2.8\right]}^{2}}{6.4^{2}}=\frac{\left(490.69)(7.84\right)}{40.96}=94$$

n1 = 94 and n2 = n1*1 = 94, Therefore, N = n1+n2 = 188

where,

m1 = mean of systolic blood pressure for the intervention group

m2 = mean of systolic blood pressure for the control group

σ1 = standard deviation of systolic blood pressure for the intervention group

σ2 = standard deviation of systolic blood pressure for the control group

n1 = sample size for group 1

n2 = sample size for group 2

α = probability of type I error (usually 0.05)

β = probability of type II error (usually 0.2)

z = critical Z value for a given α or β

N = Total sample size

By taking into account a 20% attrition rate, 226 total individuals or 113 individuals per group will be recruited for the study.

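### The primary outcome is blood pressure in the sample size, five indicators in the Methods and seven in the abstract, and the effectiveness conclusion is not tied to any one of them

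*Protocol article*

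**What the plan says.** Four places in the protocol article bear on this.

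- **Sample size.** Blood pressure is called the study's "primary outcome measure and the most common indicator of metabolic syndrome among bank employees in Bahir Dar city". A further reason given is that it yields the largest sample size of the indicators. The calculation uses systolic means and standard deviations only, and "a power of 80%, a 1:1 ratio, and a 95% confidence interval were used". The result is "n1 = 94 and n2 = n1*1 = 94, Therefore, N = n1+n2 = 188", followed by "By taking into account a 20% attrition rate, 226 total individuals or 113 individuals per group will be recruited for the study".
- **Abstract, Methods and analysis.** The primary outcomes are "change in metabolic parameters (obesity levels, blood pressure, fasting blood glucose, total cholesterol, high density lipoprotein, low density lipoprotein, and triglycerides" (closing the list). That is seven.
- **Dependent variables, Primary outcomes.** Central obesity, blood pressure, fasting glucose, HDL and triglycerides are each given a definition. That is five. The same heading also says that total cholesterol will be assayed and LDL derived, without defining either as an outcome. Both systolic and diastolic means are to be interpreted.
- **Statistical analysis.** "The effectiveness of the intervention will be assessed using differences in changes in the metabolic syndrome indicators (Obesity level, BP, FG, HDL, and TGL", compared between groups from baseline to nine months. For the quantitative data, "it will be analyzed using Stata 13.1 or later versions, with p<0.05 considered significant". No other threshold appears, and the section does not say how many of the five must differ.

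**The concern.** The sample size spends the whole two-sided 5% and the whole 80% power on one measure. The analysis section rests the effectiveness conclusion on five, and the abstract announces seven. The precedence that Sample size gives to blood pressure is not carried into the sections that define and analyse the outcomes.

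Two things are at stake. First, a reader of the final report cannot tell in advance which result settles whether the intervention worked, so the choice could be made after the results are seen. Second, the error rate of the effectiveness conclusion is undefined. It is 5% if one named outcome decides, and considerably more if any of five to seven may decide.

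The point covers the metabolic set only. Knowledge, attitudes and practice are secondary outcomes and are left aside.

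**Working it through.** **1. Reproducing the plan's figure.** Inputs from Sample size: SDs 15.0 and 16.3 mmHg, difference 114.2 − 107.8 = 6.4 mmHg, z values 1.96 and 0.84.

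n per group = (15.0² + 16.3²)(1.96 + 0.84)² / 6.4² = 490.69 × 7.84 / 40.96 = 93.9, so 94. This matches. With unrounded z values it is 95. The plan's design is therefore one systolic test at two-sided 0.05.

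**2. Counting primary outcomes.** Sample size: 1. Primary outcomes and Statistical analysis: 5, or 6 if systolic and diastolic pressure are tested separately. Abstract: 7, or 8 on the same basis.

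**3. Chance of at least one p<0.05 with no true effect, if any one result may decide.** Independent tests: 1 − 0.95^k. For equally correlated tests with correlation ρ:

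1 − ∫ φ(x) [Φ((1.96 − √ρ·x)/√(1−ρ)) − Φ((−1.96 − √ρ·x)/√(1−ρ))]^k dx

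Counting only results in favour of the intervention, independent tests give 1 − 0.975^k. The article gives no correlations, so every ρ is an assumption.

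| k | ρ = 0 | ρ = 0.3 | ρ = 0.5 | ρ = 0.7 | favourable only, ρ = 0 |
|---|---|---|---|---|---|
| 5 | 22.6% | 20.9% | 18.3% | 14.8% | 11.9% |
| 6 | 26.5% | 24.1% | 20.7% | 16.4% | 14.1% |
| 7 | 30.2% | 27.1% | 23.0% | 17.8% | 16.2% |
| 8 | 33.7% | 30.0% | 25.0% | 19.1% | 18.3% |

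The two-sided columns compare with 5%, the last column with 2.5%. An uneven assumed correlation matrix (total cholesterol with LDL 0.9, HDL with triglycerides −0.4, most other pairs 0.15) gives 21.5% for five outcomes and 26.5% for seven, by simulation.

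**4. Splitting the error instead of naming one outcome.** SE of the systolic difference at 94 per group = √(490.69/94) = 2.285, and 6.4/2.285 = 2.80.

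- α = 0.05: Φ(2.80 − 1.96) = 80%.
- α = 0.05/5 = 0.01: Φ(2.80 − 2.576) = 59%. About 140 per group would be needed for 80%.
- α = 0.05/7 = 0.00714: Φ(2.80 − 2.690) = 54%. About 150 per group would be needed.

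Both requirements exceed the 113 per group to be recruited. A Bonferroni split over the whole set would therefore give up the stated power, whereas naming one outcome would not.

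**The case against.** The strongest case against is that the percentages rest on a rule the article does not contain. A reader might infer that, as written, one significant component makes the trial positive, and so that a false claim of effectiveness is 20–30% likely. The documents do not support that. Statistical analysis says effectiveness is judged on the indicators and stops there. If all five had to be significant, the error could not exceed 5%. The two-sided percentages also count results in the harmful direction, which would not be claims of effectiveness. Counting favourable results only gives 12–16% against 2.5%. This objection stands, and it limits the figures to what could happen under one open reading.

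A reader might also infer that no outcome takes precedence. That is wrong: Sample size does give blood pressure precedence. Its remark about the largest sample size fits a different intention, namely sizing on the most demanding indicator so that the others are covered at the same α. That is a common approach, but it does not control the error across several outcomes.

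A missing multiplicity adjustment may sit in an analysis plan or full protocol that is not shown, so its absence is not the point here. Such a plan could add a method, but it would not remove the conflict over what is primary.

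The contrast of five with seven is slightly blurred, because total cholesterol and LDL are mentioned under the Primary outcomes heading. They are not defined there as outcomes and are absent from the list in Statistical analysis.

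Finally, the calculations take each single test to hold 5%. Randomization assigns two city areas by one coin toss, which puts that in doubt for every outcome, and the power figures likewise ignore clustering. That is a separate issue, and naming one primary outcome does not cure it. It does not reconcile the sections either.

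**Conclusion.** The inconsistency is certain, since it stands in the text: one primary outcome in Sample size, five in Primary outcomes and Statistical analysis, seven in the abstract, with p<0.05 as the only threshold and no statement of how many must improve.

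The consequence for the error rate is conditional. If any one significant component were read as effectiveness, the two-sided chance of a false positive would be up to about 23% (five) or 30% (seven) under independence and about 18–27% at correlations of 0.3 to 0.5. It would fall to about 15–18% only if all outcomes were strongly correlated (0.7). Counting favourable results only, it would be about 12–16% against 2.5% under independence. These figures assume that reading, the stated correlations and single tests that each hold their level.

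The point should be corrected before analysis, because it decides what the trial may conclude.

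**What to change.** Carry the Sample size choice through the article.

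- Name one primary outcome: the between-group difference in change in systolic blood pressure from baseline to nine months, using the mean of the three readings, tested at two-sided 0.05. Base the effectiveness conclusion on it. Sample size says blood pressure without specifying systolic, but systolic is the measure the trial was sized on.
- List diastolic pressure, waist circumference, fasting glucose, HDL, triglycerides, total cholesterol and LDL as secondary, reported with 95% confidence intervals and described as supportive.
- Align the abstract, Primary outcomes and Statistical analysis with this, and notify the ethics board and the registry, as Ethical considerations and declarations provides for important modifications. The registry record was not available here, so whether it already agrees is unknown.
- Do this before the month-9 data are analysed, so that the choice cannot follow the results.

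The cost is wording and a notification, with no extra participants or measurements. The real price is that an effect on another component alone could no longer be called a positive primary result.

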## Objectives

➢ To develop and test the effectiveness of a lifestyle education intervention on metabolic syndrome management among bank employees in Ethiopia.➢ To assess and compare the levels of knowledge, attitudes, and practices towards lifestyle and cardiovascular risk factors before and after the intervention as well as between the control and intervention groups among bank employees with metabolic syndrome in Ethiopia.➢ To assess the feasibility, and acceptability of an education intervention for healthy lifestyle on metabolic syndrome management among bank employees in Ethiopia.➢ To evaluate the cost-benefit of the educational intervention promoting healthy lifestyle to reduce risk factors for metabolic syndrome among bank employees in Ethiopia.➢ To evaluate the process of education intervention promoting healthy lifestyle to reduce risk factors for metabolic syndrome for bank employees in Ethiopia.

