### The status and timeline of the study

Unique Protocol ID: 2022/845 and 792/2023 in Australian National University Human Ethics Committee and College of Medicine and Health Sciences Bahir Dar University Institutional Review Board respectively.

Australian New Zealand Clinical Trials Registry: ACTRN12623000409673p

Registration date: April 24, 2023

The date recruitment began: November 20^th^, 2023.

Approximate date when recruitment will be completed: December 29, 2023 [anticipated].

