### Study timeline

The project’s enrollment, intervention, and assessment schedules are all well-established.

The enrollment started in November 2023, and the project will be closed in September 2024 (**Fig 2)**.

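### Before-after change in knowledge, attitudes and practice is listed as a basis for judging effectiveness, although it cannot separate the education from change shared by both arms

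*Protocol article*

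**What the plan says.** The Statistical analysis section sets out how effectiveness will be judged, in two steps.

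- Metabolic indicators: "The effectiveness of the intervention will be assessed using differences in changes in the metabolic syndrome indicators", compared between the groups from baseline to nine months.
- Knowledge, attitudes and practice (KAP): effectiveness is also to be judged "by assessing knowledge, attitudes, and practices towards lifestyle and cardiovascular risk factors before and after the intervention", and the sentence goes on "as well as between the control and intervention groups".

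The KAP objective under Objectives has the same two-part form: "practices towards lifestyle and cardiovascular risk factors before and after the intervention as well as between the control and intervention groups". Study design repeats it.

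A generalized linear mixed model (GLMM) is planned for the effect on the metabolic components "as well as on the knowledge, attitudes and practice of participants on healthy lifestyle". The abstract describes the purpose of these models as being to "compare the desired outcome between the trial arms, after accounting for baseline variations".

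KAP is measured in both groups at baseline and at month 9. Under Secondary outcomes, one 43-item questionnaire is named for knowledge and attitudes, with no alternate form. KAP is a secondary outcome.

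**The concern.** The subject of the passage is effectiveness. As written, a before-after rise in KAP is therefore offered as evidence of effect and not only as description. For the metabolic indicators the same paragraph uses the contrast that a controlled trial supports. The KAP wording departs from it and sets two comparisons side by side, without saying which one decides.

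Change within the education arm is the education effect plus whatever would have happened anyway over nine months. That can include familiarity with a questionnaire already answered once, and secular or calendar change. The control arm is there to remove this part, and a before-after criterion does not use it. At stake is a second route to a positive KAP claim: a significant rise in the education arm could be reported as effectiveness even if the control arm rose by the same amount.

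**Working it through.** **The plan's own figures.** The sample size section concerns systolic blood pressure: 490.69 × 7.84 / 40.96 = 93.92, so 94 per group and 188 in total; 188 × 1.2 = 225.6, so 226, or 113 per group. These reproduce. The plan gives no figure for KAP and none for a before-after comparison.

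**Timing.** Recruitment runs from 20 November to 29 December 2023. Adding nine months puts the last measurement at about 20 August to 29 September 2024, which agrees with the stated closing month, September 2024. Every before-after contrast therefore spans nine calendar months and repeats the same knowledge and attitude questionnaire.

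**What each contrast estimates.** Let δ be the education effect relative to control and s a shift common to both arms.

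- Before-after change in the education arm: δ + s
- Before-after change in the control arm: s
- Between-arm difference in change: (δ + s) − s = δ

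With δ = 0 the before-after contrast still estimates s. The between-arm contrast estimates zero, provided the shift is additive and equal in the two arms.

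**How often a before-after test would be significant with δ = 0.** Inputs:

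- Completers in the education arm: n = 90, from 113 × 0.8 = 90.4, using the plan's 20% attrition.
- Significance level: two-sided 0.05, critical value 1.96, from the plan.
- Correlation ρ between baseline and month-9 scores: assumed 0.5, with range 0.3 to 0.7.
- Shared shift s, in units of the score's SD: assumed 0.1, 0.2 and 0.3.

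In SD units the change has standard deviation √(2(1 − ρ)), so the expected z is λ = s√n / √(2(1 − ρ)). The probability of a significant result is 1 − Φ(1.96 − λ) + Φ(−1.96 − λ).

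At ρ = 0.5 the divisor is 1 and √90 = 9.487, so λ = 0.949, 1.897 and 2.846 for the three shifts.

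| Shared shift (SD) | ρ = 0.3 | ρ = 0.5 | ρ = 0.7 |
|---|---|---|---|
| 0.1 | 0.126 | 0.158 | 0.232 |
| 0.2 | 0.361 | 0.475 | 0.688 |
| 0.3 | 0.672 | 0.812 | 0.957 |

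All of these compare with a nominal 0.05. Using the 94 per group of the sample size calculation in place of 90 changes little: at ρ = 0.5 the values are 0.163, 0.492 and 0.829.

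**The case against.** The strongest reply is that the control group is not discarded. The between-group comparison stands in the same sentence, KAP is measured in both arms at both times, and the only model named for KAP is the GLMM, which the abstract presents as a between-arm comparison with baseline taken into account. The sentence could be read as one controlled pre-post comparison. No paired test is named, and details of testing may sit in an analysis plan that is not shown.

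Much of this stands. A reader might infer that KAP will be judged without the control arm; the documents do not support that. They also do not say that a significant within-arm rise alone will count as success. What remains is that before-after assessment is stated as a basis for effectiveness, in wording that differs from the controlled contrast used for the metabolic indicators in the same paragraph and that recurs in the Objectives and Study design. Nothing says the between-arm result takes precedence. If one controlled comparison is intended, a sentence would settle it.

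A reader might also infer from the dates that season biases the KAP results and that the two city areas must be measured in the same weeks. The documents do not support this either. They mention neither seasonal nor retest effects, and the dates show an interval, not a shift in scores. One recruitment window of under six weeks is given for the whole trial, and nothing suggests that the areas are enrolled at different times.

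**Conclusion.** The point holds, confined to the before-after part of the KAP criterion. That part is open to any change shared by the arms and is not valid evidence of an education effect. Under the stated assumptions, a shared shift of 0.1 to 0.3 SD would give a significant before-after result with no education effect in about 16% to 81% of trials at a correlation of 0.5, and in 13% to 96% across correlations of 0.3 to 0.7. The correlation and the shift are assumptions. The figures show how sensitive the test is to such a shift, not that one will occur. The planned between-arm GLMM comparison and the primary metabolic outcomes are not affected by a shared shift. This is a fault in the stated criterion for secondary outcomes, worth correcting because it leaves an invalid second route to a positive claim.

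**What to change.** In the Statistical analysis section and in the KAP objective, state that effectiveness on KAP rests only on the between-arm contrast from the GLMM: either the month-9 difference adjusted for the baseline score, or the group-by-time term. Report before-after change within each arm as description, without a test and without an effectiveness claim. Bring the repeated wording under Study design into line.

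The cost is a change of wording; no new data or visits are needed. The downside is that within-arm p-values are given up.

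This does not resolve a separate matter. Under Randomization, one coin toss assigns each of two city areas to an arm, so the between-arm contrast remains confounded with area. The change removes shifts common to both areas, not differences between them.
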